#### Outcome measures

The main outcome is the prevalence of prescriptions for anti-vertigo drugs. Other outcomes are the incidence of prescriptions, prevalence of long-term prescriptions, and patient and/or general practice characteristics that are associated with long-term prescriptions.

The prevalence will be calculated as the total number of patients who received at least one (long-term) prescription divided by the average number of patients between March 2018 and March 2021. The incidence will be calculated as the total number of patients with new prescriptions divided by the total number of person years in the cohort per year. A prescription will be considered ‘new’ when a period of at least 6 months has passed between the last date of the prior prescription and the first date of the new prescription. Long-term prescriptions will be defined as prescriptions for 90 days or more in 12 months’ time.

#### Analysis

We will perform descriptive statistics to determine the characteristics of patients and general practices and to calculate the prevalence and incidence of (long-term) prescriptions. A multivariable logistic regression analysis will be carried out to identify characteristics associated with a long-term prescription. We will use IBM SPSS Statistics (version 28.0) for the analyses.

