### Retrospective observational cohort study

#### Study design and data collection

We reported this retrospective observational cohort study in line with the Strengthening the Reporting of Observational Studies in Epidemiology (STROBE) Statement (Additional file 1) [25]. We will evaluate prescribing practices for anti-vertigo drugs by investigating both the prevalence and incidence of (long-term) prescriptions and characteristics associated with long-term prescriptions.

We will use anonymised routine primary care data from more than 1.2 million patients registered at 269 general practices. In the Netherlands, almost all noninstitutionalised citizens are registered with one particular GP. The included general practices participate in the Intercity Collaboration [26], which comprises academic networks of general practice at the university medical centres of Amsterdam (Academic Network of General Practice Amsterdam UMC (ANHA)), Utrecht (Julius General Practitioners’ Network (JGPN)), Groningen (Academic General Practitioner Network Northern Netherlands (AHON)), and Maastricht (Research Network Family Medicine (RFNM)). These networks run ongoing longitudinal databases containing pseudonymised data extracted from electronic patient records of the participating general practices. The databases can conditionally be used for scientific research that is relevant for (primary) care. Patients are informed about this by their GP. The databases contain data of all registered patients, except for those who objected to this (opt-out).

For this study, data will be selected from patients, aged 18 years and older, with vestibular symptoms and/or prescriptions for anti-vertigo drugs from the period March 2018 to March 2021. Patients with vestibular symptoms will be identified with International Classification of Primary Care (ICPC) codes and patients with prescriptions for anti-vertigo drugs will be identified with Anatomical Therapeutic Chemical (ATC) codes. The list of used ICPC and ATC codes is detailed in Table 1.

**Table 1 Tab1:** ICPC codes^a^ and ATC codes^b^ used for identification of patients and prescriptions

ICPC codes	ATC codes
N17 (Vertigo/dizziness)	N07CA01 (Betahistine)
N17.01 (Spinning dizziness)	N07CA02 (Cinnarizine)
N17.02 (Lightheadedness)	N07CA03 (Flunarizine)
H82 (Vertiginous syndrome)	N07CA52 (Cinnarizine, combinations)
H82.01 (Ménière’s disease)	
H82.02 (Vestibular neuritis)	
H82.03 (Benign paroxysmal positional vertigo)	

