^a^International Classification of Primary Care codes

^b^Anatomical Therapeutic Chemical codes

We will collect data on demographic characteristics, registered ICPC codes for vestibular symptoms and comorbidity, prescriptions for anti-vertigo drugs, GP consultations for vestibular symptoms, and characteristics of the general practices (e.g. degree of urbanisation). Table 2 shows an overview of the variables, including those that are used for the interrupted time series (phase 3.1).

**Table 2 Tab2:** Overview of variables for retrospective observational cohort study (phase 1) and interrupted time series (phase 3)

	**Variable**	**Definition**
**Patient characteristics**	Age	In years at time of registration ICPC code for vestibular symptoms
	Sex	Male or female
	Diagnosed vestibular disorder	According to ICPC code (see Table 1)
	Comorbidity	According to the following ICPC codes: K86 (Hypertension uncomplicated), K87 (Hypertension complicated), K83 (Heart valve disease), K84 (Heart disease other), K75 (Acute myocardial infarction), K76 (Ischaemic heart disease without angina), T90 (Diabetes), K89 (Transient cerebral ischaemia), K90 (Stroke/cerebrovascular accident), P74 (Anxiety disorder/anxiety state), P76 (Depressive disorder), A49.02 (Polypharmacy)
**General practice characteristics**	Registered patients	Total number of patients registered at practice per year and total number of adult patients (aged 18 years and over) registered at practice per year
	Employed general practitioners	Total number of general practitioners per year with patients registered to their name
	Degree of urbanisation	Based on 4-digit postal code: not/hardly urbanised (< 1.000 surrounding addresses), moderately urbanised (1.000–1.500 surrounding addresses), strongly urbanised (1.500–2.500 surrounding addresses), and extremely urbanised (> 2.500 surrounding addresses)
**Other**	Date of registration ICPC code for vestibular symptoms	-
	Date of registration and deregistration at general practice	-
	Referral for vestibular rehabilitation^a^	As described in electronic patient record
	Prescription for anti-vertigo drug	According to the ATC code (see Table 1)
	Date of prescription	-
	Referrals to physiotherapist, ENT specialist, neurologist, and/or geriatrician^a^	As described in electronic patient record
	GP consultations	Total number of GP consultations (all types of consultations, including telephone consultations and home visits) per patient per year for vestibular symptoms

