#### Analysis

Descriptive statistics will be used to assess the usage and characteristics of participants. In addition, we will perform a mixed-effects logistic regression analysis to evaluate whether these characteristics are associated with successful treatment. We will use IBM SPSS Statistics (version 28.0) for the descriptive statistics and the mixed-effects logistic regression analysis will be performed with R software (version 4.2.1).

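### The Phase 1 regression on long-term prescribing names no term for the 269 practices; fitted as written, it would give too-narrow intervals for practice-level characteristics

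*Protocol article*

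**What the plan says.** The relevant statements are in Phase 1, Retrospective observational cohort study, unless another section is given.

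- **Data (Study design and data collection).** The source is "more than 1.2 million patients registered at 269 general practices", drawn from four academic networks.
- **Target (Outcome measures).** Among the other outcomes are "patient and/or general practice characteristics that are associated with long-term prescriptions". The binary outcome is fixed as follows: "Long-term prescriptions will be defined as prescriptions for 90 days or more in 12 months’ time".
- **Practice variables (Table 2).** Registered patients, number of employed GPs and degree of urbanisation are listed as general practice characteristics.
- **Model (Analysis).** "A multivariable logistic regression analysis will be carried out to identify characteristics associated with a long-term prescription". Software: "We will use IBM SPSS Statistics (version 28.0) for the analyses". No random effect, GEE or cluster-robust error is named.
- **Contrast (Phase 3, Prospective observational cohort study, Analysis).** For users of the application, "we will perform a mixed-effects logistic regression analysis to evaluate whether these characteristics are associated with successful treatment".

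**The concern.** Urbanisation is the same for every patient of a practice, and so, within a given year, are list size and number of GPs. If patients of one practice resemble each other in whether they receive long-term prescriptions, each further patient from that practice adds less information about such a characteristic than an independent patient would. An ordinary logistic model counts every patient in full.

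The article gives reason to expect some resemblance. In the Discussion it assumes that one GP who attends an audit and feedback meeting affects all patients registered at that practice. That does not supply a correlation, but it makes a value of exactly zero implausible.

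At stake is a practice feature being reported as associated with long-term prescribing when the data do not support it. The Phase 1 introduction says that results of this phase will be used to tailor the implementation strategy.

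**Working it through.** The article states no sample size, correlation or interval for this regression, so there is no figure of its own to reproduce. What can be checked is how large the error would be if the named model were fitted as an ordinary logistic regression.

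**Inputs from the article.** 269 practices and 1.2 million patients: 1,200,000 / 269 = 4,461 registered patients per practice.

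**Assumed inputs, not in the article.** Between 0.5% and 3% of registered patients enter the regression: 4,461 × 0.005 = 22, × 0.01 = 45, × 0.03 = 134 per practice. The within-practice correlation (ICC) is 0.02 to 0.05.

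**Formulas for a covariate constant within practice.** Design effect DEFF = 1 + (m − 1) × ICC. The ordinary standard error is too small by √DEFF. The true error rate of a nominal 5% test is 2 × [1 − Φ(1.96 / √DEFF)].

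| m | ICC | DEFF | √DEFF | Error rate, formula | Error rate, simulated |
|---|---|---|---|---|---|
| 22 | 0.02 | 1 + 21 × 0.02 = 1.42 | 1.19 | 10% | 7.8% |
| 22 | 0.05 | 1 + 21 × 0.05 = 2.05 | 1.43 | 17% | 12.5% |
| 45 | 0.02 | 1 + 44 × 0.02 = 1.88 | 1.37 | 15% | 11.3% |
| 45 | 0.05 | 1 + 44 × 0.05 = 3.20 | 1.79 | 27% | 23.5% |
| 134 | 0.02 | 1 + 133 × 0.02 = 3.66 | 1.91 | 31% | 24.3% |
| 134 | 0.05 | 1 + 133 × 0.05 = 7.65 | 2.77 | 48% | 41% |

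The last column comes from 400 simulated data sets per row, with 269 practices, an assumed 30% outcome frequency and a practice covariate with no effect.

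**Which covariates are affected.** A separate simulation used 269 practices of 45 patients, 300 data sets per setting and a baseline log-odds of −1.4 (about 20% with the outcome). It gave this coverage of nominal 95% intervals:

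| ICC | Ordinary model, practice-level covariate | Robust / ordinary SE |
|---|---|---|
| 0 | 95% | 1.00 |
| 0.02 | 91% | 1.21 |
| 0.05 | 81% | 1.48 |
| 0.10 | 70% | 1.87 |

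In the same data, a patient-level covariate varying within practice kept 93% to 96% coverage at every ICC. Cluster-robust standard errors restored the practice-level coverage to 95% to 97%.

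**Why this simulation gives less than the formula.** Its ICC is on the latent logit scale. At ICC 0.05 the between-practice variance is 0.05/0.95 × π²/3 = 0.173. With an outcome frequency p of about 0.198, the correlation on the observed scale is roughly p(1 − p) × 0.173 = 0.159 × 0.173 = 0.0275. Then DEFF = 1 + 44 × 0.0275 = 2.21 and √DEFF = 1.49, in line with the simulated 1.48. The two calculations therefore agree once the scale is matched.

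**Wider assumptions.** With 0.5% to 4% of patients analysed and an ICC of 0.01 to 0.10, the formula gives DEFF from 1.21 to 18.7, a standard-error factor of 1.10 to 4.33, and coverage from 92.5% down to 35%.

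**The case against.** The strongest objection is that the defect is read from silence. The article never says that the model is single-level or that patients will be treated as independent. A multivariable logistic regression could carry a random intercept or robust errors, the named software can fit such models, and a condensed article may leave the variance estimation to a fuller plan. It stands that an ordinary fit is an inference. It remains the natural reading, because the same article names a mixed-effects logistic model where it wants one.

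Three further limits also stand:

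- **The regression as a whole is not compromised.** A reader might infer that all its intervals are too narrow. Most candidate covariates in Table 2 (age, sex, diagnosis, comorbidity codes) are patient-level, and the simulation shows almost no loss for those that vary within practice. Patient covariates that themselves cluster by practice would fall in between.
- **The information does not shrink to 269 units.** A reader might infer this from the number of practices. The design effects above imply an effective number of about 269 × 22 / 2.05 = 2,900 to 269 × 134 / 3.66 = 9,800 patients.
- **The route to a wrong decision is weak.** The main Phase 1 outcome is prevalence, and the effect of the implementation is evaluated in Phase 3. Phase 2 already describes a final strategy, and none of its components is targeted by urbanisation, list size or number of GPs.

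A small point: Table 2 defines list size and number of GPs per year, so they may shift somewhat within a practice over the three-year window. They remain shared by all its patients in any one year.

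**Conclusion.** The point holds in a conditional and limited form. If the Phase 1 regression is fitted as the ordinary model that the text names, intervals for practice-level characteristics will be too narrow, and false positives for them too frequent, at any positive within-practice correlation. With 22 to 134 patients per practice and a correlation of 0.02 to 0.05, standard errors are understated by a factor of about 1.2 to 2.8. A nominal 5% test then rejects a true null in about 8% to 41% of simulated data sets (10% to 48% by formula). These sizes rest wholly on assumed inputs, and at zero correlation there is no loss.

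The article does not support the claim that clustering has been deliberately ignored or that the patient-level results are unsound. Severity is moderate: this is a secondary Phase 1 outcome, and the error does not reach the Phase 3 evaluation.

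**What to change.** In Phase 1, Retrospective observational cohort study, Analysis, replace the named model with a mixed-effects logistic regression with a random intercept per practice. Alternatively, keep the logistic model and fit it by GEE clustered on practice, or with cluster-robust standard errors by practice. State which is chosen, because the random-intercept model gives practice-specific odds ratios and the other two give population-averaged ones.

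Adding network as a fixed effect and reporting the between-practice variance would be informative, but neither is needed to cure the problem.

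The change is one of wording. It needs no new data, and the named software can fit it. The cost is wider intervals for practice characteristics.

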### Qualitative interview study

#### Study design and data collection

We reported this qualitative interview study using the consolidated criteria for reporting qualitative research (COREQ) (Additional file 2) [27]. We will identify barriers and facilitators of behaviour change, i.e. decreasing anti-vertigo drug use/prescriptions and increasing VR use/referrals, in GPs and patients with vestibular symptoms by conducting semi-structured interviews. We will conduct these interviews before start of the implementation in April 2023. Recruitment of GPs will take place through general practices that are connected to the ANHA, and through the professional network of the research group members. Patients will be recruited through the recruited GPs and the patient association (Hoormij•NVVS). We will inform GPs and patients who are interested and gather their characteristics for purposive sampling. For GPs, we will seek diversity in age, gender, years of practice, location of practice, size of practice, and prescribing behaviour for anti-vertigo drugs. For patients, we will seek diversity in age, gender, place of residence, education level, diagnosed vestibular disorder, and usage of anti-vertigo drugs.

We will obtain informed consent before the interview. Interviews will last approximately 30 min and will take place online, at the patients’ home/at the general practice, or at Amsterdam University Medical Centre. We will use a topic guide developed with the Theoretical Domains Framework and COM-B model [28, 29]. All interviews will be audio-recorded and transcribed verbatim. Interviews will be conducted until data sufficiency is reached.

#### Outcome measures

In the interviews with GPs, we aim to understand why they prescribe anti-vertigo drugs and what barriers and facilitators GPs may see when they stop prescribing anti-vertigo drugs.

In interviews with patients, our goal is to identify reasons for using anti-vertigo drugs and barriers and facilitators that may arise when they stop using these drugs.

#### Analysis

We will use a thematic analysis approach, according to Braun and Clarke, for the analysis of the transcripts [30]. Transcripts will be divided into fragments and codes will be assigned to these fragments by two independent investigators. After the first few interviews, codes will be discussed by the two investigators and, when consensus is reached about the coding scheme, the remaining interviews will be coded. Subsequently, the investigators will identify themes and codes will be assigned to these themes. In the final stage, themes from different transcripts will be compared and we will search for relations. All findings will be discussed with the research group. To facilitate the analysis, MaxQDA 2022 will be used.

## Phase 2: nationwide implementation of Vertigo training

We will embed Vertigo Training in Dutch primary care from April 2023 onwards. The online application will be made freely available through the website www.gezondheidsmeter.nl. More information on Vertigo Training is described in Table 3.

**Table 3 Tab3:** Information on intervention to be implemented: Vertigo Training

Vertigo Training is a freely accessible internet-based intervention that contains six exercises. These six exercises include eye, head, and body movements that aim to stimulate vestibular compensation, a process in which the nervous system reorganises and is able to overcome damage of the vestibular system. In addition, a form of exposure-based behavioural therapy takes place by deliberately provoking vestibular symptoms in a controlled environment. The application prescribes a personal exercise regimen based on the severity of symptoms while performing the exercises. Patients are asked to perform the exercises twice a day for 10 min. The regimen lasts 6 weeks. Patients can start with Vertigo Training on their own initiative, or they can be referred to the treatment by a healthcare provider. They can perform the exercises by themselves, but it is also possible to receive support from a healthcare provider, such as a physiotherapist. In the Netherlands, patients can access physiotherapy through self-referrals.
Patients are eligible for Vertigo Training if they are 18 years and older, if they have had vestibular symptoms for at least one month during most days of the week, and if these symptoms are provoked or exacerbated by head movements or visual stimuli.

We created an implementation plan, involved local implementation specialists, and identified relevant stakeholders (i.e. GPs, ENT specialists, physiotherapists, and patients with vestibular symptoms) to adapt our implementation strategy to their needs. The final strategy consists of the following components: guideline adaptations; mass and target marketing strategy; pharmacotherapeutic audit and feedback meetings (PTAMs); education for GPs, patients, and physiotherapists; clinical decision support; and local champions. We will elaborate on these components further on.

We used the Standards for Reporting Implementation Studies (StaRI) Statement to report the implementation strategy and the intervention (Additional file 3) [31].

### Multicomponent implementation strategy

The strategy contains the following components:Guideline adaptationsThe Dutch College of General Practitioners’ clinical guideline for vestibular symptoms will include a recommendation for internet-based VR together with a hyperlink to Vertigo Training. In addition, a hyperlink to this intervention will be included in regional transmural agreements.Mass and target marketing strategyWe will generate national attention for chronic vestibular symptoms and the intervention using mass media (e.g. press releases, newspapers, radio and television shows, and social media). To reach healthcare providers, we will collaborate with Dutch medical journals. We will also collaborate with the patient platform Thuisarts.nl, the most popular visited medical website by patients nationwide [32]. This platform will inform patients about VR, provide instructions for the exercises, and add a hyperlink to Vertigo Training. Furthermore, the patient association will actively inform their members about the availability of the intervention. Lastly, we have developed an infographic that contains information on Vertigo Training. GPs can use this infographic in their waiting room and consulting room to maximise exposure to patients and as a reminder to the availability of the intervention. This infographic will be disseminated through media channels and along with the guideline for PTAMs.Pharmacotherapeutic audit and feedback meetingsWe will provide guidelines for PTAMs as a way to encourage GPs to stop prescribing anti-vertigo drugs and start referring patients to (internet-based) VR. In the Netherlands, these meetings are regularly organised by pharmacists and GPs in order to improve evidence based prescribing behaviour. GPs will see how they perform compared to their peers using anonymised prescription data extracted from electronic patient records. We will actively promote the PTAM guidelines to general practices connected to the academic general practice networks.Education for GPs, patients, and physiotherapistsWe will offer free education to GPs (in training), patients, and physiotherapists (in training) to improve their knowledge on chronic vestibular symptoms and VR. For instance, we will develop an e-learning module and host webinars.Clinical decision supportWe aim to add automatic recommendations for (internet-based) VR to electronic patient records. This recommendation would show up when a GP registers a vestibular ICPC code as a way to support them in choosing VR (instead of anti-vertigo drugs).Local championsWe aim to recruit GPs from different regions throughout the Netherlands to act as local champions. Their role will be to encourage colleagues to use (internet-based) VR and to organise PTAMs. Furthermore, we will motivate local champions to start their own additional implementation activities.

## Phase 3: Evaluation of the implementation

The evaluation will take place in three ways:

### Interrupted time series

#### Study design and data collection

An interrupted time series compares longitudinal data before and after an intervention. This design can be used when a RCT is not affordable or possible and is especially useful for evaluating interventions in real world settings, such as in our case [33]. Therefore, this design has been widely used for evaluating changes in health policy and interventions that aim to improve health system quality [33, 34].

For this part of the study, we will also use anonymised routine primary care data from the Intercity Collaboration as described in the retrospective observational cohort study from phase 1. In this case, we will compare data from adult patients with vestibular symptoms and/or prescriptions for anti-vertigo drugs from the period before (April 2021–March 2023) and after (April 2023–March 2025) implementation to determine whether the implementation changed how GPs treat patients with vestibular symptoms and to explore the effectiveness of the individual components of our strategy.

Patients with vestibular symptoms and/or prescriptions for anti-vertigo drugs will be identified using ICPC codes and ATC codes that are detailed in Table 1. We will gather data on demographic characteristics, registered ICPC codes for vestibular symptoms and comorbidity, prescriptions for anti-vertigo drugs, GP consultations for vestibular symptoms, referrals for VR, and referrals to physiotherapy and secondary care. We will also gather information on the characteristics of the general practices. An overview of variables, including their definitions, can be found in Table 2.

